### Testing the data collection process

We will collect data among 5 participants to help us (i) assess for clarity of study questionnaires (ii) identify any barriers to data collection and study implementation and (iii) figure out ways of circumventing the barriers to study implementation if any. The data from these 5 participants will not be included in the final analysis.

### The intervention

After discharge, the program manager will link the participants with a VHT nearest to them. The participants (randomized to the intervention arm) will be informed during the consent procedure that they will undergo 6 psycho-education sessions (1 per month) together with a family member at the participant’s residence. The VHTs and participants will meet and schedule appointments for the next engagements. This shall be done on a case by case basis. Some psycho-education sessions could take place in the patient’s residence, others in the nearest public space (school or church or mosque compounds). We will document where the majority of these sessions happen. This will help us document feasibility. The PI and RAs will sit in some of the sessions during the pilot phase of data collection to ensure fidelity to the manual.

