### Hypothesis

We hypothesize that (i) we will recruit 70% of eligible participants and accrue a sample size of 80 over 20-weeks, retaining 80% of the sample size for 24 weeks, (ii) the intervention will lead to improvement in clinical outcomes in patients with FEP (see above).

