#### Random sequence allocation

We will use a simple random technique to randomize participants. Random numbers that determine which study arm the participant will be in will be generated by an independent statistician who will not be part of the study team.

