#### Blinding participants and RA to the study arm

Participants will be randomly assigned to the study arms. The RA and participants will all be blinded to the study arm they will be allocated before consent. VHTs will deliver 6 psycho-education sessions (1 per month) to participants in intervention arm and their family members at the participant’s residence. The PI and RAs will sit in some of the sessions during the first 2–3 sessions of data collection to ensure fidelity to the manual. We will conduct 5 exit focus group discussions with patients and family members to assess acceptability to the use of the manual. Participants in the control arm will get usual treatment. RA’s will schedule participants from both arms for an assessment using the same instruments at weeks 4, 12 and 24 at the clinic. We will have a separate set of RA’s for the intervention arm and another for the control arm to ensure blinding of the RA.

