#### The informed consent procedure

The RA’s will invite potential participants to take part in the study and obtain written informed consent. During the consenting process, the purpose of the study will be described further, the procedures will be explained, the benefits and risks of taking part in the study will be outlined. Upon demonstrating understanding and being given a chance to ask questions, the potential participant will then provide a witnessed, signed or thumb print consent. Caregivers will also be required to provide written informed consent, since we will collect demographic information from them.

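### The description of the intervention reads as if the arm is known and disclosed during consent, which conflicts with the rule that research assistants and participants are blinded to the arm before consent

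*Protocol article*

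**What the plan says.** Two statements in the protocol article bear directly on the point.

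- The intervention: "The participants (randomized to the intervention arm) will be informed during the consent procedure that they will undergo 6 psycho-education sessions". The rest of that section covers practical matters such as linkage to a village health team member, scheduling and venue.
- Blinding participants and RA to the study arm: "The RA and participants will all be blinded to the study arm they will be allocated before consent".

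The informed consent procedure names the research assistants (RAs) as the people who "will invite potential participants to take part in the study and obtain written informed consent". The RA is therefore both the person taking consent and the person the blinding rule covers.

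**The concern.** The sentence on the intervention limits the information to people described as already randomised to one arm, places its delivery within the consent procedure, and states the sessions as a settled fact rather than a possibility. A patient told this knows the arm before deciding whether to join, and so does the RA who says it. The blinding section rules that out.

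Two things would be at stake if staff worked from the literal sentence.

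- **Between-arm comparisons.** Data analysis plans compares the arms on retention, adherence, stigma, illness management and symptom severity. Sample size estimation says the data will yield an effect size for a powered trial. If patients accept or decline knowing their arm, or the RA's approach varies with it, the enrolled groups may differ for reasons other than chance. The intention-to-treat analysis named in the Abstract does not help, because the selection happens before anyone is enrolled.
- **The recruitment proportion.** The first hypothesis is that "we will recruit 70% of eligible participants and accrue a sample size of 80 over 20-weeks, retaining 80% of the sample size for 24 weeks". If some patients are asked to accept sessions and others to accept usual care, the share who enrol is a blend of two uptakes. A later trial needs to know how many eligible patients will agree to be randomised, and the blend does not estimate that.

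**Working it through.** No arithmetic applies. The point concerns the order of three events (consent, allocation and disclosure of the arm) and depends on no rate, power or sample size. The check is to read every section that could fix that order.

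1. **The intervention.** Literal order: randomised, then consent under way, then arm disclosed. Disclosure comes before consent is complete.
2. **Blinding participants and RA to the study arm.** Neither the RA nor the participant knows the arm before consent. Disclosure cannot come before the decision.
3. **Random sequence allocation.** The article says "We will use a simple random technique to randomize participants", with numbers "generated by an independent statistician who will not be part of the study team". This settles the method and the source of the sequence. It does not say when an individual's arm is released, so it supports neither order over the other.
4. **The informed consent procedure.** One procedure is described for all potential participants, in which "the purpose of the study will be described further, the procedures will be explained", followed by benefits and risks. Telling a candidate the allocated arm is not listed. This fits the blinding rule better than it fits the literal sentence in step 1, but it does not say that the arm is withheld.
5. **Data collection and Ethical considerations.** Both order information, consent and the capacity check. Neither places randomisation in that sequence. Ethical considerations refers to the consent form in the singular.

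Steps 1 and 2 cannot both hold at the moment the patient decides. Steps 3 to 5 do not state the release point. Steps 4 and 5 suggest which order was meant, without settling it.

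**The case against.** The strongest reply is that the sentence is loosely written and means only this: candidates are told at consent that those randomised to the intervention will have six sessions. It sits in a section about logistics, not in the sections that govern consent or allocation. Those sections describe one consent procedure and one form, and the blinding section states the rule outright. This reply carries weight. It makes a drafting slip the likelier explanation, and it means the literal order should not be treated as the intended procedure. It does not remove the conflict, because the sentence does not say this and someone writing a consent script could follow it as it stands.

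A narrower reply is that the blinding rule covers the time before consent while disclosure comes during it, so the two meet without overlapping. That does not work. Consent is given at the end of the procedure, and a rule that lapsed when the conversation began would not protect the decision it is there to protect.

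A reader might go further than the text allows in three ways.

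- *That the trial allocates before consent by design, so concealment is broken.* The article presents no such choice, and the blinding section rejects it.
- *That consent content differs by arm.* Only the parenthesis in one sentence suggests this. No other section mentions arm-specific consent.
- *That the separate RA teams for the two arms would reveal the arm at consent.* The article mentions these teams directly after the follow-up assessments and does not say that they take consent.

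**Conclusion.** The inconsistency is real and should be corrected. As worded, the description of the intervention has the arm known and disclosed during consent, against the article's own blinding rule, and no other section states when the arm is released.

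The consequences are conditional. Selection bias in the arm comparisons and a recruitment proportion that mixes two offers would follow only if the sentence were carried out literally and if willingness to enrol, or the RA's approach, varied with the arm. The document gives no acceptance rates by arm, so the size cannot be estimated, and any figure would rest on invented rates. The clinical comparisons are secondary and described as preliminary. Recruitment is one part of the primary objective; retention is the other.

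It would be tempting to add that the article should also fix when baseline assessment takes place relative to randomisation. The two statements do not conflict on that, and such sequencing is commonly left to the full protocol, so it is not part of this point.

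**What to change.** Reword the sentence in The intervention to agree with the blinding section. It should say two things:

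- every candidate hears the same description of both arms during consent, including that those allocated to the intervention would have six sessions;
- the arm is released to the RA and the participant only after consent is complete.

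If the consent form or script has arm-specific wording, replace it with the common text. The cost is a sentence or two in the protocol and, where needed, identical consent wording for both arms. No staff, visits or participants are added. If the milder reading was intended all along, practice does not change and only the sentence needs correcting.

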### Follow-up

Participant Follow-up: We shall collect the same data as at baseline from participants at month 3 then every six months. If the participant accesses health care and we are not aware, we will review their medical records and abstract information collected during the course of routine care (where they exist). However, all attempts will be made to always collect data directly from the participants.

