**Data analysis:**

We will document the proportion of participants who consent and get recruited, the proportion of those who will get retained and reasons for drop out. We will conduct an intention to treat analysis comparing the groups at weeks 4, 12, 24 and assess the effect of the intervention on the clinical outcomes (described above). We will use the Bonferroni approach to correct for multiple comparisons.

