### Data analysis plans

We will report the duration of recruiting participants and the proportion of eligible patients who get recruited. We will compare the demographic parameters (age, gender, education status) as well as disease severity. We will compare the proportion of participants who are retained in the study at week 4, 12 and 24 as well as mean differences in adherence, stigma, illness management ability and symptom severity (PANSS or YMRS) scores between the intervention and control arms. We will use the Bonferroni approach to correct for multiple comparisons.

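### The Follow-up section's visit schedule (month 3, then six-monthly) conflicts with the weeks 4, 12 and 24 on which the assessments, analyses and retention target rely

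*Protocol article*

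**What the plan says.** The protocol article gives two schedules for the study assessments.

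- Follow-up: the baseline data are to be collected again "at month 3 then every six months".
- Blinding participants and RA to the study arm: "RA’s will schedule participants from both arms for an assessment using the same instruments at weeks 4, 12 and 24 at the clinic".

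The rest of the article works with the second. The data analysis paragraph of the abstract says "We will conduct an intention to treat analysis comparing the groups at weeks 4, 12, 24". Data analysis plans compares the "proportion of participants who are retained in the study at week 4, 12 and 24", together with mean differences in adherence, stigma, illness management and symptom scores. The hypothesis, in the abstract and in the introduction, speaks of "retaining 80% of the sample size for 24 weeks".

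Table 1 does not settle the matter: its second column is labelled only as follow-up, without times. Nothing in the article ranks one schedule above the other, or says that the Follow-up section describes a longer, separate phase.

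**The concern.** This is a contradiction in the current text, not a detail left to a fuller document. A site working from the section that carries the name Follow-up would book different visits from a site working from the blinding section.

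Two things are at stake. The score comparisons at weeks 4 and 24 need assessments at those weeks. Week 24 is also about when the course of six monthly sessions ends, so it is the natural end-of-intervention comparison. In addition, retention at 24 weeks is half of the primary objective, and it is most cleanly counted at a study visit that both arms are due to attend. The Community tracing section starts home tracing by reference to the last scheduled appointment, so it also depends on which schedule is in force.

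**Working it through.** **Inputs.** Follow-up section: month 3, then every six months. Blinding section, abstract and Data analysis plans: weeks 4, 12 and 24. Hypothesis: 80 participants, 80% retained for 24 weeks, so 0.80 × 80 = 64.

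**Conversion.** A calendar month is 365.25 / 12 / 7 = 4.348 weeks. Equating month 3 with week 12 implies 4-week months, so both conventions are shown. The Follow-up sentence can be read in two ways.

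| Reading of the Follow-up sentence | Months | Weeks, calendar months | Weeks, 4-week months |
|---|---|---|---|
| Literal: six-month steps after month 3 | 3, 9, 15 | 13.0, 39.1, 65.2 | 12, 36, 60 |
| Six-monthly marks counted from baseline | 3, 6, 12 | 13.0, 26.1, 52.2 | 12, 24, 48 |

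**Comparison with weeks 4, 12 and 24.**

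- Week 4: no visit on either reading. The first visit is at week 12 or 13.
- Week 12: matched by month 3 on both readings, to within about a week.
- Week 24, literal reading: no visit. The next one comes 39.1 − 24 = 15.1 weeks later with calendar months, or 36 − 24 = 12 weeks later with 4-week months.
- Week 24, from-baseline reading: month 6 falls at week 24 to 26, so a visit is held at or up to about two weeks after the horizon.

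**Beyond the horizon.** Both readings also produce visits after 24 weeks (from month 9 or month 12) for which neither the hypothesis nor the analysis section has a use.

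No power or sample size figure enters this check, and none changes with the correction.

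**The case against.** The strongest reply is that the Follow-up sentence is one outlier against a consistent plan. The blinding section names who schedules, which arms, which weeks and where. The abstract, hypothesis and analysis section all share the 24-week horizon. Harm arises only if staff follow the outlier and set the explicit instruction aside. This stands as a limit on the likely damage, but it does not remove the contradiction, since the article gives no order of precedence.

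A reader might infer that 24-week retention could not be measured at all under the Follow-up section, so that the primary outcome would be lost. The documents do not support that. Study measurements provides standardized forms for attendance at monthly clinic review. The Follow-up and Medical record review sections allow abstraction from charts, and Community tracing adds telephone and home contact. A 24-week count could be assembled from these sources.

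It would be less direct. Clinic attendance measures remaining in care, whereas the analysis section compares remaining in the study. Session completion is recorded in the intervention arm only. Medical record review itself foresees that control participants may come for care and be missed by the research assistant.

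Nor can one say flatly that no visit falls near week 24: that is true of the literal reading but not of the from-baseline reading. Only the loss of week 4 holds on both.

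**Conclusion.** The contradiction is real and must be reconciled. The Follow-up sentence omits week 4 on every reading and week 24 on the literal one, where the next visit falls 12 to 15 weeks after the horizon. If it were followed, the planned comparisons of adherence, stigma, illness management and symptom scores would have no data at the missed weeks. On the literal reading, 24-week retention would rest on attendance forms or records instead of a study visit common to both arms.

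The conclusion about week 4 needs no assumption. The conclusion about week 24 assumes that the six-month steps start at month 3, and the 12-to-15-week range reflects only the choice of 4-week or calendar months. The practical consequence assumes that the Follow-up section, rather than the blinding section, is the one put into practice.

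**What to change.** Replace the sentence in Follow-up with study assessments at weeks 4, 12 and 24 in both arms, matching the blinding section, the abstract and Data analysis plans. Then either delete the six-monthly visits or state that they form a separate extension beyond the 24-week trial.

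The cost is a change of wording. It adds no visit to those already set out in the blinding section, alters no sample size figure, and concerns the timing of research assessments rather than clinical care.

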### Medical record review

There is a possibility that participants in the control arm will return to access care at the facility and be missed by the RA. They could also be admitted to the facility due to other health complications. We will review participant’ medical charts and abstract information about any admission to the hospital, duration of stay, laboratory parameters, and any other recorded complications.

### Adverse event reporting during participant follow-up

We anticipate that this project will have minimal adverse events that are directly related to the study. However, if we observe any adverse events as a result of the use of prescribed medications during clinical care or loss of privacy/confidentiality, then we will report it promptly to the relevant regulatory bodies per requirement. Confidentiality could be broken in the event that the RA gets information related to the following: a) participant is suicidal, b) participant threatens to commit a homicide, and c) participants reports a sexual abuse to themselves or other parties. The RA will immediately inform the PI about such, and appropriate action will be taken including reporting such cases to the administration of Butabika Hospital.

#### Potential risks

There is a potential risk of developing severe psychological distress during the interviews as a result of answering questions that are deemed private by the participant. RA will be trained to identify any of such distress, and the interview will be terminated. Participants may be asked to continue with the interview only if they feel like doing so. Such adversities will be reported to the PI and SOMREC. There is also a risk of having information about participants made available in the public domain. We will guard against this by having all identifying information of the patients locked away in file cabinets and password locked computers. The risk to loss of information is minimal.

#### Benefits

There are no direct monetary benefits to be gained by the individuals. However, participants will receive regular assessments for their symptoms for the study period. Those in the intervention arm will receive psycho-education sessions. Furthermore, participating in this study will also help scientists to learn more about what predicts relapse in patients with psychosis.

#### Community tracing

If a participant has not appeared for a clinic visit on their scheduled clinic appointment, we will contact them or their appointed person through telephone. If neither the patient nor the contact person can be reached by phone three months from the last date of their scheduled appointment, we will make active attempts to trace the participant at their residence by liaising with the VHT based in the same location. If the participant can’t be traced at their place of residence, we will consider them as a potential loss to follow-up. There exists several village health team members who provide care to non-mental health clients. We will utilize their knowledge about the village to identify individuals in the cohort.

### Data analysis plans

We will report the duration of recruiting participants and the proportion of eligible patients who get recruited. We will compare the demographic parameters (age, gender, education status) as well as disease severity. We will compare the proportion of participants who are retained in the study at week 4, 12 and 24 as well as mean differences in adherence, stigma, illness management ability and symptom severity (PANSS or YMRS) scores between the intervention and control arms. We will use the Bonferroni approach to correct for multiple comparisons.

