### Sample size estimation

Being a study assessing feasibility of recruitment as a primary outcome, we have not conduced a formal sample size and power calculation. Rather, we have considered that recruiting 70% of potentially eligible participants over a 20-week period and retaining 80% of recruited participants will provide us with adequate data that will be needed in recruiting participants for a powered RCT.

In 2018 [41], a total of 43,870 individuals accessed care at the hospital, 60% (26,322) of them were diagnosed with psychotic disorders, approximately 20% (5,264) of the 26,322 patients with psychosis presented for the first time (potential cases of FEP). Thus, the number of participants who are eligible for recruitment is approximate 440 per month. Close to 20% of the Ugandan population lives within the central districts from where we intend to recruit participants—we anticipate having 88 patients (with psychosis) eligible for recruitment per week. However, a significant proportion of patients present with a psychosis resulting from substance use. We anticipate that approximately 40% of the 88 patients would be eligible as per criteria described below. Thus, we will have approximately 32 participants eligible for recruitment per week with a recruitment target of 24 of the 32 participants per week. We will document what proportion of this figure is attained.

With a sample size of 80 participants, we will be able to conduct preliminary analyses to detect modest significant differences (5% increase in mean scores) in illness self-management and adherence as well as a 5% reduction in mean stigma and symptom severity. We will use this data to generate an effect size that can be used in a sample size estimation of a powered RCT.

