#### Data collection

The health care providers based in the wards from where we will collect data will be informed about the study. They will identify patients who may be eligible and refer them to the RA for a second round of eligibility screening. The RAs shall provide potential participants with information about the study, obtain written informed consent, then administer the University of California, San Diego Brief Assessment of Capacity to Consent (UBACC) [42] to assess participant comprehension of the consent process.

RA’s will administer a) standardized questionnaire to collect demographic and clinical variables (age, gender, address, education, date of symptom onset) from the patients. We will collect demographic information in the form of age, gender, address and education from care givers. b) Feasibility measures (number of eligible participants who accept to enroll in the study, number of participants who are retained in care over study duration, number of participants who adhere to prescribed intervention, duration of recruitment of participants, reasons for decline to enroll in the study as well as reasons for dropping out of the study), c) MINI to confirm a diagnosis, d) Young Mania Rating Scale (YMRS) [43] for individuals with bipolar illness or Positive and Negative Symptoms of Schizophrenia Scale (PANSS) [44] for individuals with schizophrenia spectrum disorders to assess symptom severity e) World Health Organization Disability Assessment Schedule, f) Internalized Stigma of Mental Illness scale to assess for stigma, g) a medication adherence measure to assess for adherence h) Illness Management and Recovery (IMR) [45] scale to document the ability of patients to manage their illness and (i) care giver burden using the short version of the burden scale for care givers (BSFC) [46].

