
**Table 1 pone.0268493.t001:** Summary of the study instruments to be administered at baseline and follow-up.

Instrument	Baseline	Follow-up
Consent forms, UBACC(administered a day earlier)		
Demographic parameters	Yes	No
UBACC	Yes	No
MINI	Yes	Yes
Physical exam	Yes	Yes
Symptom severity using the YMRS/PANSS	Yes	Yes
GASS	Yes	Yes
WHODAS 2.0	No	Yes
Medication adherence using the MARS	No	Yes
WHO Audit to assess all course mortality	No	Yes
Illness Management and recovery	No	Yes
BSFC (participant’s care givers only)	Yes	Yes

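### The symptom-severity comparison should state whether and how it uses the baseline PANSS or YMRS score

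*Protocol article*

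**What the plan says.** *Data analysis plans* names the quantity to be compared: "mean differences in adherence, stigma, illness management ability and symptom severity (PANSS or YMRS) scores between the intervention and control arms". The abstract adds the timing and the analysis set: "We will conduct an intention to treat analysis comparing the groups at weeks 4, 12, 24". Neither place mentions a baseline covariate, a change score or a model.

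Table 1, under *Study measurements*, has the row "Symptom severity using the YMRS/PANSS", marked Yes at baseline and Yes at follow-up. Which scale a participant gets depends on diagnosis (*Data collection*): "Young Mania Rating Scale (YMRS) [43] for individuals with bipolar illness or Positive and Negative Symptoms of Schizophrenia Scale (PANSS) [44] for individuals". The second scale is the one for the schizophrenia spectrum group.

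The only other mention of severity in the analysis section is "We will compare the demographic parameters (age, gender, education status) as well as disease severity". That sentence does not say at what time or between which groups.

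On allocation, *Random sequence allocation* says "We will use a simple random technique to randomize participants", and no stratification is mentioned. On purpose, *Sample size estimation* says "We will use this data to generate an effect size that can be used in a sample size estimation of a powered RCT".

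**The concern.** Symptom severity is the efficacy outcome for which the article clearly schedules a pre-intervention score. The described analysis gives that score no role. With 80 people allocated by simple randomisation, the arms can differ by chance in baseline severity. A comparison that ignores baseline carries part of that chance difference into the estimated effect and has a larger variance than the data allow.

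The protocol intends to use the estimated effect when sizing the next trial. Avoidable noise in the pilot estimate would therefore pass into that sample size.

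**Working it through.** **The plan's own figure.** *Sample size estimation* says: "With a sample size of 80 participants, we will be able to conduct preliminary analyses to detect modest significant differences (5% increase in mean scores" and so on for the other outcomes. This cannot be reproduced, because no SD, significance level or power is given. With 40 per arm and two-sided alpha 0.05, a normal approximation gives 80% power at a standardised difference of (1.960 + 0.842) × √(2/40) = 0.626. A 5% difference in means reaches that only if the SD is at most 0.05/0.626, or about 8% of the mean. The figure does not show whether a baseline term was assumed.

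**Inputs.**
- From the protocol: 80 participants, planned as 40 per arm; 80% retention at 24 weeks, so about 32 per arm.
- Assumed: baseline-to-follow-up correlation ρ of 0.3, 0.5 or 0.6; equal SDs at both times; and, for illustration only, one common scale in SD units. The protocol gives no ρ, no SD and no split by diagnosis.

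**Variance under the three readings of a mean difference**, relative to raw follow-up scores:
- raw follow-up: 1
- change from baseline: 2(1 − ρ)
- adjusted for baseline (ANCOVA): 1 − ρ²

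| ρ | Raw | Change | Adjusted | Cut, adjusted v. raw |
|---|---|---|---|---|
| 0.3 | 1 | 1.40 | 0.91 | 9% |
| 0.5 | 1 | 1.00 | 0.75 | 25% |
| 0.6 | 1 | 0.80 | 0.64 | 36% |

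Adjustment is at least as precise as either alternative, apart from the degree of freedom it uses. Change scores only equal raw scores at ρ = 0.5 and are worse below it. The recommendation therefore does not depend on which reading was intended.

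**Precision with 32 per arm.** SE = √(2(1 − ρ²)/32) in SD units.
- Raw: √(2/32) = 0.250, 95% half-width 1.96 × 0.250 = 0.49.
- ρ = 0.3: SE 0.238, half-width 0.47; 64 patients act like 64/0.91 ≈ 70.
- ρ = 0.5: SE 0.217, half-width 0.42; 64/0.75 ≈ 85.
- ρ = 0.6: SE 0.200, half-width 0.39; 64/0.64 = 100.

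**Illustrative power**, two-sided alpha 0.05, noncentral t, 32 per arm, with the adjusted analysis losing one degree of freedom:

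| Assumed effect | Unadjusted | ρ = 0.3 | ρ = 0.5 | ρ = 0.6 |
|---|---|---|---|---|
| 0.5 SD | 50% | 54% | 62% | 69% |
| 0.71 SD | 80% | 83.5% | 90% | 94% |

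These figures pool two scales. Within PANSS or YMRS alone the groups are smaller and absolute power is lower, by an amount that cannot be computed without the diagnostic split. For a given ρ the proportional variance cut is unchanged.

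**Chance baseline difference.** With 40 per arm its SD is √(2/40) = 0.224 SD units. The probability that it exceeds 0.3 SD in either direction is 2 × [1 − Φ(0.3/0.224)] = 2 × [1 − Φ(1.34)] = 18%. A difference of 0.3 SD shifts the raw follow-up contrast by 0.3ρ: 0.09 SD at ρ = 0.3, 0.15 SD at ρ = 0.5.

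**Effect on the next trial.** For an assumed true effect of 0.5 SD, n per arm at 80% power is 2 × (1.960 + 0.842)²/0.5² ≈ 63. A chance imbalance of one SE moves the raw estimate by 0.224ρ. At ρ = 0.3 that is 0.067, which gives 49 to 84 per arm; at ρ = 0.5 it is 0.112, which gives 42 to 105.

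**The case against.** The strongest objection is that a short analysis section in a journal article need not name its covariates. Baseline adjustment is ordinary content of a statistical analysis plan or full protocol, and neither is shown. A between-arm mean difference is also what ANCOVA or a mixed model delivers, so the wording is compatible with adjustment. This stands. A reader might infer that the plan has fixed a raw follow-up comparison and throws the baseline away, but the text is silent and does not say so.

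A reader might also infer that baseline severity will be tested for significance between arms. The sentence on disease severity names no test, time or groups, so that does not follow either.

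Three further limits stand:
- Under randomisation a chance imbalance is random error, not bias, and adjustment removes only the part that baseline explains.
- Patients enter with symptoms resolved and are stable enough for discharge (*Eligibility criteria*). The restricted range may lower ρ, and at ρ = 0.3 the gain is modest.
- Efficacy is a secondary, preliminary objective. Even at ρ = 0.5 the half-width falls only from 0.49 to 0.42 SD, so the effect size stays imprecise for planning.

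The point should not be extended to the other outcomes. Table 1 marks adherence and illness management as not taken at baseline and does not list the stigma scale, whereas *Data collection* and *Follow-up* can be read as saying that the same data are collected at baseline. Symptom severity is the secure case.

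None of this removes the recommendation. The article does name the contrast, the outcomes, the visits and the multiplicity method. One more clause would settle how a score already being collected is used.

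**Conclusion.** The point holds as a recommended clarification and improvement. The article describes the symptom comparison without any role for the scheduled baseline score and leaves open whether the difference is raw, change or adjusted. Adjustment would cut the variance by 9% to 36% for ρ between 0.3 and 0.6, relative to raw scores. That range is assumed, and the low end is plausible here.

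The power and sample-size figures are illustrations for a single pooled scale and should not be quoted as properties of this trial. The documents do not support a claim that the planned analysis is biased or invalid. If the analysis plan already specifies baseline adjustment by scale, what remains is to bring the article's wording into line with it.

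**What to change.** In *Data analysis plans*, state that symptom severity is compared between arms adjusted for the participant's own baseline score on the same scale, by ANCOVA or by a mixed model over weeks 4, 12 and 24. Say how the two scales are handled: either separate models for PANSS and YMRS, or scores standardised within scale in one model with a term for scale.

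Report the adjusted between-arm difference with its 95% CI. Alongside it, report the unadjusted SD and the baseline-to-follow-up correlation, so that the powered trial can be sized to match its own analysis. Use the residual SD for that purpose only if that trial will also adjust for baseline; otherwise its sample size would be too small.

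Cost: a few lines of text, one or two degrees of freedom and slightly more analysis work. Separate models also mean fewer patients per model. No new data, visits or participants are needed.
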